### 13. Data Safety and Monitoring

The Data Safety and Monitoring Board (DSMB) will oversee and provide advice to the PIs on the continued scientific integrity and safety of the implementation of the trial. At each meeting the board will review the status of recruitment, retention, successes, barriers and challenges of the implementation of the trial, adverse events and the reporting procedures of adverse events. Two interim analyses will be conducted in addition to the planned “final” analyses at the conclusion of the proposed study. These interim analyses will be conducted when 33.3% and 66.7% of the planned sample size have passed their 12-month follow-up assessment time point window. The DSMB will review findings from the interim analysis and determine whether the study needs to be terminated for safety reasons. Data will be sent to the DSMB a week prior to the meeting. The Board will meet twice a year. The meetings will be face-to-face. Minutes taken at the meeting will be archived. We have included a statement in the DSMP that the proposed Board members have no Conflict of Interest with the study. The DSMB will consist of four expert members in the field who are experienced with HIV treatment, substance abuse treatment, and vulnerable populations. The DSMB will meet twice a year. The DSMB will consist of three expert members in the field who are experienced with HIV treatment, substance abuse treatment, and vulnerable populations. Specifically the members will include:

1. [name], is the Senior Director of the Substance Abuse Treatment Evaluations and Interventions Research Program at RTI International. Since its inception in 1999, this program has evolved to include a multimillion dollar yearly portfolio. She is also

Adjunct Professor at the School of Public Health at UNC, Chapel Hill, and Adjunct Associate Professor of Psychiatry at Duke University School of Medicine. She has conducted multiple NIH-funded clinical trials testing gender specific HIV interventions with different populations of women drug users.

2. [name], is a Professor of Epidemiology and Public Health at Columbia University School of Public Health. He is an expert in addiction medicine and HIV care among drug users. [name] is an Associate Professor of Biostatistics at University of Pennsylvania. She is an expert in developing data analytic plans and analyzing outcome data for clinical trials and will perform the interim analyses.

3. [name] is a Professor of Medicine at SUNY Downstate Medical Center. He has extensive experience conducting clinical research with HIV-infected women drug users.

**Interim Analyses and Stopping Rules:** Two interim analyses will be conducted in addition to the planned final analyses at the conclusion of the proposed study. These interim analyses will be conducted when 33.3% and 66.7% of the planned sample size (N=140 and N=280 women respectively) have passed their 12-month follow-up assessment time point window. Several considerations and/or constraints were balanced in deciding upon key aspects of interim analyses. We restricted the number of interim analyses to 2 in order to prevent too great a threat to valid statistical inference due to a theoretical need to adjust analyses to avoid Type I error inflation from multiple comparisons using the same data. Interim analyses will be conducted at the selected information rates (i.e., the 33.3% and 66.7% values) based on 12-month follow-up duration period as per recommendations in *Methodological Challenges in Biomedical HIV Prevention Trials* published in 2008 by the Institute of Medicine (IOM). Specifically, in the chapter entitled *Interim Monitoring and Analysis of Results*, the IOM recommended that stopping HIV prevention trials based on positive interim results should require evidence of a sustained impact. Thus, interim analyses will utilize complete data over the longest follow-up duration, i.e., the 12-month assessment time point. The Principal Investigators and Co-Investigators will be unblinded to the research, whereas the study staff will be blinded to the interim analysis. The interim analysis will be conducted by the statistician on the study and the results will be reported to the PIs. With respect to efficacy, stopping rules following an interim analysis focus on demonstrable benefit among the sample and data accrued to date.

At each interim time point as well as after study completion, analyses will follow the data analysis plans for primary aims described in the original proposal. Interim analyses will focus on the study's primary aims. If at any of the interim analyses the statistical significance for all biological outcomes related to primary aims (i.e., cumulative STI incidence), exceeds the a priori  $\alpha < .05$  criterion at that time point, the study will be stopped since the inference will be that significant benefit of assignment to one study arm over the other will have already been demonstrated. We note that this represents two-sided hypothesis testing since demonstrating benefit with respect to disease prevention of one intervention over the other (regardless of the content of that intervention) is of public health value and importance. With respect to futility, stopping rules are concerned with effect size estimates indicating a null result is inevitable given the planned total sample size. Stopping a study in such circumstances avoids additional expenditure of time, fiscal, and human resources that would nevertheless ultimately result in lack of evidence of superiority of one intervention over the other. At each interim analysis time point, a post hoc power analyses will be conducted to determine the minimum sample size needed to achieve 80% power to reject the null hypothesis given point estimates and standard errors of efficacy estimates using data collected to date. If the estimated minimum sample size for power analyses using  $\alpha =$

.05 exceeds the planned enrollment of N=420 women for all of the biological and self-reported behavioral outcomes associated with the primary aims, the investigative team will notify the NIDA Program Official (PO) of such findings. Based on the magnitude of the difference between the estimated minimum sample sizes needed for 80% power and targeted sample size, in addition to recruitment rates to date, the investigative time and NIDA PO will discuss and agree whether the study should be stopped due to reasons of futility or whether modifications to the study design/protocols (e.g., increasing planned enrollment, hiring of additional recruitment staff, etc.) can be implemented to avoid futility.

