### 1.2. Primary Aims

1. To test the comparative effectiveness of E-WORTH versus Streamlined HIV Testing on primary outcomes of decreasing biologically confirmed STIs and the number and proportion of unprotected sexual acts at the 12-month follow-up and secondary outcomes of reducing drug use, increasing utilization of drug treatment, linkage to HIV care and ART adherence (for HIV+ participants), decreasing partner violence and recidivism.
2. To test if the effectiveness of E-WORTH on study outcomes is moderated by client characteristics (e.g. client subgroups defined by socio-demographics and psychosocial characteristics)
3. To estimate the costs and comparative cost-effectiveness of E-WORTH versus Streamlined HIV Testing on STI infection rates, drug use and projected number of HIV cases averted at the 12-month follow-up.

4. To examine qualitatively and quantitatively how multi-level theory-driven factors may influence the fidelity of implementation and effectiveness of E-WORTH and Streamlined HIV testing on study outcomes.

1.3 Rationale: Despite extremely high rates of HIV and STIs that have been found among women on probation, parole or ATI programs nationwide, to date, WORTH is the only intervention that has been found to be efficacious in increasing condom use and reducing sexual risks among justice involved women in the U.S. Our recent study of 337 drug-involved women on probation or community supervision in NYC found that 17% of the 221 Black women tested positive for HIV and 30% tested positive for an STI . The HIV rate found among Black women on probation indicates a highly concentrated epidemic, comparable to rates in sub-Saharan Africa; however, no HIV prevention or testing services are provided in NYC probation sites. The proposed study will address this critical gap in services for Black women drug users in probation settings by testing the effectiveness and cost-effectiveness of the 5-session multimedia E-WORTH intervention.

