**2.3 Power Analyses:** From ICC estimates based on the previous WORTH trial, variance inflation factors were calculated to generate effective sample sizes used in G\*Power for Aim 1. For cumulative STI incidence, we assumed a 50% reduction (on a background cumulative incidence of 20.5%) to be clinically meaningful to detect via Poisson regression; for behavioral outcomes, projected means, standard deviations, allow for effect size  $f^2$  to be calculated and used in G\*Power. Results for primary outcomes (Figure 3) indicate that 80% power is achieved for the rate-limiting outcome (i.e., cumulative STI incidence) with an effective sample size of 372 participants; translating to a sample size of 378 participants after accounting for ICC. We then increased the starting sample size to 420 to safeguard against attrition (modeled as a complete loss of 10% of data as conservative estimate since the efficacy trial of WORTH achieved a 91% retention rate at 12-month follow-up and many of those cases provided data at earlier assessment points, thus were not “fully” missing). For secondary outcomes, power analyses participants/arm indicate 80% power to detect differences for effect sizes  $f^2 = .03$  to  $.04$  (for  $\alpha = .1$  TO  $.5$ ) with sample sizes as low as 369.

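### The 140-woman efficacy look can stop the trial on about 19 STI events, where almost every significant result overstates the planned 50% reduction.

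*Supplement*

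**What the plan says.** Protocol section 13 (Interim Analyses and Stopping Rules) schedules two interim looks, when "N=140 and N=280 women respectively) have passed their 12-month follow-up assessment time point window". If the biological primary outcome, cumulative STI incidence, meets the .05 criterion at either look, "the study will be stopped since the inference will be that significant benefit of assignment to one study arm over the other" is taken as shown. The test is described as two-sided. The section limits the looks to two because of Type I error, but gives no boundary or spending function. Interim and final analyses follow the same plan.

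Section 2.3 sets the planning values: "we assumed a 50% reduction", "on a background cumulative incidence of 20.5"%, and "80% power is achieved for the rate-limiting outcome" "with an effective sample size of 372 participants; translating to a sample size of 378 participants after accounting for ICC". A 10% loss then brings the total to 420. The Data Analyses Plan tests new STI at 12 months by logistic regression.

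Neither section sets a minimum number of events for an efficacy stop, or says how the effect is estimated or its interval formed after an early stop.

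**The concern.** A rule that stops on significance at a small look selects large estimates. The fewer the events, the larger the observed effect must be to pass, and the more an estimate from a stopped trial exceeds the truth. This happens when E-WORTH works, and it is distinct from the false-positive rate.

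At stake is the size of the main STI result. Aim 3 also covers "comparative cost-effectiveness of E-WORTH versus Streamlined HIV Testing on STI infection rates", so an inflated STI effect could carry into the economic results. The protocol does not spell out how the STI effect enters that analysis, so this second consequence is an inference.

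**Working it through.** **Inputs.** Section 2.3: control incidence 20.5%, reduction 50% (so 10.25%), loss 10%. Section 13: looks at 140 and 280 women, two-sided .05 at each. Section 3.5 (Randomization): equal allocation.

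**The plan's own figure.** Poisson regression with a 1:1 binary covariate: n = (1.96 x sqrt(4) + 0.8416 x sqrt(6))^2 / (0.205 x (ln 0.5)^2) = 35.78 / 0.0985, about 364. An unpooled two-proportion formula gives 382. Both are within 3% of the stated 372. 378 / 0.9 = 420 exactly.

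**Events at the first look.** 140 x 0.9 = 126 women, 63 per arm. 63 x 0.205 + 63 x 0.1025 = 12.9 + 6.5 = 19.4. With no loss: 70 x 0.3075 = 21.5.

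**What reaches .05 at that count (two-sided p).**

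| Control v E-WORTH | Per arm | Reduction | Chi-square | Logistic | Poisson | Fisher |
|---|---|---|---|---|---|---|
| 13 v 6 | 63 | 54% | .081 | .088 | .117 | .134 |
| 14 v 5 | 63 | 64% | .025 | .031 | .048 | .044 |
| 15 v 7 | 70 | 53% | .063 | .069 | .096 | .103 |
| 16 v 6 | 70 | 62% | .020 | .025 | .040 | .035 |

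Holding the control arm at exactly 20.5% instead, the smallest significant reduction is 60% (chi-square), 61.5% (logistic) or 66% (Poisson) with 63 per arm, and 57%, 58.5% or 63% with 70 per arm. Hence the range 57-66%.

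**Estimate given a first-look stop for benefit.** Simulated trials with 63, 126 and 189 women per arm, pooled z above 1.96, reduction = 1 - (E-WORTH events / control events):

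| True reduction | Stop at first look | Median estimate there |
|---|---|---|
| 50% | 35% | 69% (IQR 62.5-75%) |
| 35% | 18% | 64% |
| 25% | 11% | 62% |

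At a true 50%, only 0.3% of these stops show a reduction of 50% or less. Across chi-square, logistic and Poisson tests, with or without loss, the stop probability runs from 27% to 39% and the mean estimate given a stop from 68% to 72%. Averaged over all three looks, the mean estimate is about 54%.

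**Second look.** Expected events are 126 x 0.3075 = 38.7 with loss and 140 x 0.3075 = 43.1 without. The smallest significant reduction (logistic, control at 20.5%) is 45% or 43%, below the planned 50%.

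**Effect of a 40-event minimum.** At a true 50%, the mean estimate over all looks falls from about 54% to 49.6% and power stays near 81% (83% under the current rule). With no effect, the chance of any significant result falls from about 10.4% to 7.6%.

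**The case against.** Several points on the other side stand.

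- **64% is not a floor.** A reader might infer from the 14 v 5 split that nothing smaller can stop the trial. Event counts vary: at a true 50% with 63 per arm, 28% of first-look stops (chi-square) fall below 64%.
- **The plan does not say it will report the naive estimate.** It names ordinary logistic regression and the same analysis at every look, and is silent on estimation after a stop. The supportable statement is that no stopping-adjusted estimate is named.
- **The final estimate need not rest on 19 events.** At 14 women a month (section 2.1), the 140th enters after about 10 months. At least 12 months later about 22 x 14 = 308 are enrolled. Stopping the study need not end their follow-up. With 10% loss they would give 308 x 0.9 x 0.15375, about 43 events, and the median estimate after a first-look stop would be about 60% at a true 50%. The bias shrinks but remains, and the protocol does not say whether these women are followed and included.
- **The average bias is small**, about 4 points at a true 50%. The harm is conditional on an early stop.
- **It stems largely from the unadjusted .05.** With an O'Brien-Fleming-type first boundary (z about 3.47), first-look stops at a true 50% fall from 35% to about 2%. That makes such a stop rare; it does not correct the estimate when one occurs.

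A reader might also expect a median-unbiased estimate to repair a first-look stop. Under stagewise ordering, a stop at the first look has the same tail probability as a fixed-sample test, so estimate and interval equal the naive ones. For 14 v 5 (z = 2.24) nothing changes. The correction acts only from the second look on.

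**Conclusion.** The concern holds in a limited form. At the 140-woman look, the stopping rule acts on about 19 events (22 without loss), and almost every stop for benefit there would show more than the planned 50%: typically near 70% when the truth is 50%, and about 62% when the truth is 25%. Under the planning assumption, roughly one trial in three would stop there.

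This rests on the 20.5% incidence applying to the 12-month outcome, equal arms, the unadjusted .05, and an estimate drawn from the women analysed at that look. The documents do not support a claim that the trial's result is badly biased on average, or that an inflated figure is certain to be reported. The gap is that nothing prevents a stop on so few events, and nothing says how the effect would then be estimated.

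**What to change.** In section 13, allow no efficacy stop until a minimum number of STI events has accrued, for example about 40, roughly the number expected at the 280-woman look. The 140-woman look would then serve other purposes but not stop for efficacy.

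In section 13 and the Data Analyses Plan, state that after a stop at the second look or later a median-unbiased estimate with a stagewise-ordering interval is reported beside the usual estimate. State also whether women enrolled but not yet at 12 months are followed to 12 months and included.

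The cost is wording, a little analysis work, and a later earliest efficacy stop. The exact number needs thought: with 10% loss and a true 50% reduction, the second look expects 38.7 events (SD = sqrt(126 x 0.205 x 0.795 + 126 x 0.1025 x 0.8975) = 5.7), so a strict 40 would be met there in only about 45% of trials. A slightly lower figure would still exclude the first look.

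No change to the interim model's covariates is needed for this point; it would set the interim analysis apart from the final one. The event minimum does not by itself restore the .05 error rate (7.6% remains), which is a separate matter.

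### Comparative interim results go to the Principal Investigators, whose team then acts on them, and the interim analyst's role is described inconsistently

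*Supplement*

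**What the plan says.** All of this is in the protocol, Section 13, Data Safety and Monitoring. Both protocol copies in the supplement carry the same arrangement.

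- **Access.** "The Principal Investigators and Co-Investigators will be unblinded to the research, whereas the study staff will be blinded to the interim analysis". The next sentence reads: "The interim analysis will be conducted by the statistician on the study and the results will be reported to the PIs".
- **Analyst.** The list of DSMB members includes a biostatistician at an outside university, of whom it says: "She is an expert in developing data analytic plans and analyzing outcome data for clinical trials and will perform the interim analyses".
- **DSMB role.** "The DSMB will review findings from the interim analysis and determine whether the study needs to be terminated for safety reasons". The section opens by giving the board a wider advisory role covering scientific integrity as well as safety. It also records that "the proposed Board members have no Conflict of Interest with the study".
- **Content of the looks.** Cumulative STI incidence is tested at two-sided .05 for efficacy. For futility, a required sample size is calculated "given point estimates and standard errors of efficacy estimates using data collected to date".
- **Use of the results.** If that sample size exceeds 420 for all the biological and behavioural primary outcomes, "the investigative team will notify the NIDA Program Official (PO) of such findings". The two parties then agree whether to stop or to change the design, for instance by enrolling more women.

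**The concern.** In an open behavioural trial the investigators may well know who is in which arm. Knowing the difference between the arms while the trial runs is another matter. Here the PIs are told that difference, and the investigative team uses it to decide, with the funder, whether to stop or enlarge the trial. The plan blinds study staff to the interim analysis, so it recognises the risk of leakage, yet it exempts the people above them.

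At stake is whether later decisions can be shown to be independent of the trend. Such decisions include a change in sample size, the relatedness of an adverse event, a protocol change, and the form of the final model. Once the comparison has been seen, that independence cannot be restored.

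The uncertainty over who runs the analysis adds to the problem. If it is the trial's own statistician, the person fitting the final model may also have seen the interim result.

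**Working it through.** **1. The statements side by side (Section 13).**

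| Question | DSMB paragraphs | Interim Analyses and Stopping Rules |
|---|---|---|
| Who runs the look? | Outside-university biostatistician listed with the DSMB | The study's statistician |
| Who receives it? | DSMB | PIs (Co-Investigators also described as unblinded) |
| Who decides on safety? | DSMB | Not stated |
| Who decides on efficacy? | Not stated | A .05 criterion, no decision-maker named |
| Who decides on futility? | Not stated | Investigative team with the funder's program official |

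Nothing reconciles the first two rows, and nothing separates the by-arm results from the investigators.

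**2. What the informed people still decide.**
- Futility stopping or a larger enrolment (Section 13).
- Whether an adverse event is study-related, and, in a review every two months, whether adverse events warrant protocol changes (Section 12).
- The final model. Section 2.2 selects covariates by their significance with outcome and attrition and by differences between arms. The Data Analyses Plan selects sociodemographic covariates on imbalance or literature, and leaves Poisson or negative binomial open for the count of condomless acts.

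**3. The plan's own interim sizes.** 420 × 1/3 = 140 and 420 × 2/3 = 280. Both match Section 13.

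**4. How much of the trial follows the first look.** Inputs from Section 2.1: recruitment starts in month 14 at an average of 14 women per month. From Section 13: the look comes when 140 women have passed the 12-month window.
- The 140th woman enrols after 140 / 14 = 10 months, at month 24.
- With no lag before follow-up starts, the look falls at month 24 + 12 = 36.
- Enrolled by then: 14 × (36 − 14) = 308. Remaining: 420 − 308 = 112.

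Follow-up is counted from the end of the intervention, so some lag is likely. Section 3.5 (Randomization) refers to a 28-day period for filling a group, and four group sessions follow. The documents give no figure for the lag. For an assumed lag of L months, the number remaining is 112 − 14L:

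| L (months) | Look 1 at month | Still to enrol |
|---|---|---|
| 0 | 36 | 112 |
| 1 | 37 | 98 |
| 2 | 38 | 84 |
| 3 | 39 | 70 |

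The number of 12-month windows still open does not depend on L: 420 − 140 = 280, or 280 / 420 = 67%. It is an upper figure, because some women will be lost.

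**5. Second look.** 280 / 14 = 20 months, so month 34, plus 12 = month 46 at the earliest. Since 14 × 32 = 448 exceeds 420, planned enrolment would be complete. Up to 420 − 280 = 140 windows (33%) would be open.

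**The case against.** **Safeguards that exist.** Study staff are blinded to the interim analysis. The STI outcome is a DNA amplification assay run by an outside laboratory (Section 3.5, Biological Assays). Behavioural outcomes are collected by ACASI, assignment is by a randomization program, and efficacy stopping follows a fixed criterion. This stands: the routes by which an informed PI could distort outcome measurement are narrow. It does not reach the decisions listed in step 2 of the working.

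**Two statisticians.** A reader might infer that two different people are assigned the same analysis. Names are removed and the two descriptions could fit one person. Her place on the board is itself unclear: the text gives both four and three members, and she appears within the second of three numbered entries. What is shown is an inconsistent role.

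**Direct supervision.** A reader might also infer that the PIs supervise recruiters, facilitators, retention and quality assurance. The protocol does not say so. Sections 3.1 and 3.8 give recruitment and tracking to research assistants, and Section 3.9 refers to facilitator supervision without naming the PIs. The nearest support is the weekly recruitment summaries sent to the PI and Project Director (Section 9).

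**A safety-only DSMB.** The board's advisory remit is wider than safety, and it does receive the interim findings. What is missing is a stated role in the efficacy and futility decisions.

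**Co-Investigators.** The explicit reporting line is to the PIs. Co-Investigator access rests on the unblinding sentence and on the investigative team's part in the futility discussion.

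**Conclusion.** The point holds in this form. As written, the plan gives comparative interim results to the PIs and describes the Co-Investigators as unblinded. It has the investigative team act on the efficacy estimates with the funder, and it leaves unclear whether the analyst is independent of the trial. That is an avoidable exposure to operational and analytic bias, and it should be closed before the first look.

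The extent is roughly 70 to 112 women still to be enrolled at the first look and up to 280 of 420 twelve-month windows open. These figures rest on recruitment at the planned 14 per month and an assumed lag of 0 to 3 months. They measure how much of the trial would run after the investigators know the trend. They do not measure a bias, and the documents give no basis for estimating one. No stated sample size changes.

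**What to change.** Replace the two sentences in Section 13 that unblind the investigators and assign the analysis to the study's statistician. The new text should state that:

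- the biostatistician listed with the DSMB, independent of trial conduct and of the final analysis, runs the interim comparison;
- only the DSMB sees results by arm;
- the DSMB reviews the efficacy and futility criteria already in Section 13, as well as safety;
- the PIs and the funder receive only a recommendation to continue, stop or modify, and act on that.

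The same edit should settle whether the board has three or four members and whether the biostatistician is one of them.

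The cost is modest, because a board, a conflict-of-interest statement and a biostatistician are already in the plan. It is more than wording, however. The funder's program official is now a party to the futility decision and must agree to the revised process. The PIs and the funder would also lose direct sight of the interim estimates when they discuss futility. The section has no formal futility boundary, only the comparison of a re-estimated sample size with 420, so the DSMB would weigh that comparison rather than apply a fixed rule.

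### Under the planned effect the STI-only stopping rule ends about two trials in three early, and the 80% power stated for secondary outcomes makes no allowance for this

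*Supplement*

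**What the plan says.** Aim 1 (section 1.2) names biologically confirmed STIs as primary together with "the number and proportion of unprotected sexual acts at the 12-month follow-up and secondary outcomes of reducing drug use", and goes on to drug treatment, HIV care, partner violence and recidivism.

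Section 13 plans two interim analyses, when 140 and 280 women have passed their 12-month window. The efficacy trigger is cumulative STI incidence alone. The rule opens "If at any of the interim analyses the statistical significance for all biological outcomes related to primary aims (i.e., cumulative STI incidence" and continues: if that significance "exceeds the a priori $\alpha < .05$ criterion at that time point", then "the study will be stopped since the inference will be that significant benefit of assignment to one study arm over the other" is taken as shown. The test is two-sided: "We note that this represents two-sided hypothesis testing". No other outcome enters the efficacy rule, and the level is the same at each look. The futility rule in the same section does require all primary biological and self-reported behavioral outcomes to point the same way before the funder is notified.

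Section 2.3 states: "For secondary outcomes, power analyses participants/arm indicate 80% power to detect differences for effect sizes" f² of .03 to .04, "with sample sizes as low as 369". Neither that sentence nor the rest of section 2.3 mentions the interim analyses. Section 13 does not say whether stopping ends enrollment only, or also the follow-up of women already randomized.

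**The concern.** The stated secondary power is a full-size figure, but the stopping rule makes full size the less likely outcome if E-WORTH works on STIs as planned. In that case the drug use, partner violence and recidivism comparisons may rest on fewer women than the power statement assumes. A null secondary result after an early stop would then be read against 80% when the true figure may be well below it. The behavioral primary outcomes are exposed in the same way, but their loss cannot be calculated because the figure that holds their power results is not shown.

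**Working it through.** **Inputs.** From section 2.3: STI 20.5% versus 10.25%; 372 effective, 378 after ICC, 420 after 10% attrition; secondary 80% at N as low as 369. From section 13: looks at 140 and 280 women past 12 months, two-sided .05 at each. From section 2.1: accrual of 14 per month from month 14. Allocation is 1:1 (section 3.5, Randomization).

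**The plan's own figures.** A two-sided Poisson calculation with null variance at the base rate gives 363 in total, within 3% of 372. A two-proportion test at 186 per arm has 78.5% power. 378/0.9 = 420. For secondary outcomes, f²=.03 at N=369 gives 80.2% as a 3-df F test and 91.3% as a 1-df test. The number of predictors is not stated. The main calculation therefore takes 80% at 369 at face value, which is equivalent to f²=.0214 on one df.

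**Chance of stopping.** At the first look with n per arm,

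power = Φ{[(p₁−p₂) − 1.96√(2p̄(1−p̄)/n)] / √([p₁(1−p₁)+p₂(1−p₂)]/n)}.

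With n=70 and p̄=.15375: (.1025 − .1195)/.0604 = −.28, so 39%. With n=63 (10% attrition): 36%. Simulated binomial data with the score test (400,000 runs) give:

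| | 10% attrition | no attrition |
|---|---|---|
| Stop at look 1 | .350 | .391 |
| Stop at look 2 | .302 | .310 |
| Reach full size | .349 | .298 |

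Early stopping is thus 65-70%. A normal approximation gives 66-70%.

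**Who is randomized at each look.** 140 women are enrolled by month 14 + 140/14 = 24 and pass 12 months at month 36. By then 22 × 14 = 308 are enrolled. 280 women pass at month 14 + 20 + 12 = 46. Enrollment of 420 takes 30 months and ends at about month 44. Follow-up is timed from the end of the intervention, so the true counts at each look are if anything higher.

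**Secondary power by stage** (noncentral F, 1 df, noncentrality f²N, 80% at 369):

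| Women analyzed | Power |
|---|---|
| 126 / 140 (look 1, past 12 months only) | .371 / .405 |
| 252 / 280 (look 2, past 12 months only) | .638 / .684 |
| 277 / 308 (look 1, all randomized followed) | .68 / .73 |
| 378 / 420 (full size, or look 2 with all followed) | .810 / .849 |

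**Averages over stopping stage.**

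- Only women past 12 months, 10% attrition: .350×.371 + .302×.638 + .349×.810 = .60.
- Only women past 12 months, no attrition: .391×.405 + .310×.684 + .298×.849 = .62.
- All randomized women followed, 10% attrition: .350×.68 + (.302+.349)×.810 = .77 with these rounded inputs, .76 unrounded.
- All randomized women followed, no attrition: .391×.73 + (.310+.298)×.849 = .80.

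If f²=.03 is a 1-df test, the same averages are about 73-74% and 88-91%.

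**With an O'Brien-Fleming-type boundary** (critical values 3.471, 2.454, 2.004): stops fall to .020 + .409 = .43 with 10% attrition and .028 + .444 = .47 with none. The low-end average becomes .020×.371 + .409×.638 + .571×.810 = .73, and .028×.405 + .444×.684 + .527×.849 = .76.

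**The case against.** A reader might infer that the rule ends the trial at 140 or 280 women. The documents do not support that. Those are counts of women past 12 months, and on the planned accrual about 308 and then all 420 are already randomized. A look-2 stop cannot shrink the randomized sample. If the women in the pipeline are followed, average power is 76-80%, close to what section 2.3 states. The Data Analyses Plan also models behavioral outcomes over the whole follow-up period, so 3- and 6-month data from women short of 12 months could contribute even without further follow-up. The 60-62% is therefore the low end of a range and cannot be stated without its condition.

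The 80%-at-369 calibration is also one reading of a garbled sentence. With f²=.03 on one df, all the figures are higher. Finally, sections 1.1 and 2.1 call STI incidence the primary outcome, so stopping on it alone is a defensible choice.

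All of this stands, and it limits the size of the point. It does not remove it. The plan nowhere says that randomized women continue, and it bases efficacy stopping on the data accrued so far at 12 months. Even when all are followed, a look-1 stop (35-39% likely) leaves 68-73% power on the face-value calibration.

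**Conclusion.** The point holds as a mismatch between two sections. Section 13 makes an early stop likely under the planned effect, and section 2.3 gives a secondary power that is valid only at full size. On the face-value calibration the average is 60-62% or 76-80%, depending on a follow-up rule the plan leaves out. On the 1-df reading of f²=.03 the low end is 73-74%, and with follow-up the average (88-91%) exceeds the stated 80%.

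These figures assume the planned STI effect, attrition of 0-10%, and secondary estimates independent of the STI estimate. With a correlation of 0.3 the low-end average is 63-66%. A reader might also conclude that a trial stopped this way cannot answer the rest of Aim 1. The documents do not support that, since the loss may be small if randomized women are followed.

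**What to change.** 1. In section 13, replace p<.05 at each look with a conservative boundary. An O'Brien-Fleming type would be about p<.0005 at 140 and p<.014 at 280, with the final critical value adjusted to match (2.004). Early stopping falls from 65-70% to about 43-47%, and the low-end secondary average rises to about 73-76%.
2. In section 2.3, state that 80% for secondary outcomes holds only if the trial reaches full size. Give the figures after a look-1 and a look-2 stop, each with its analysis set: 37-41% and 64-68% if only women past 12 months are analyzed, or 68-73% and 81-85% if all randomized women are followed. State the number of predictors behind f² so that one calibration can be chosen.

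The cost is wording in two sections, a less favorable power statement, and early stopping that happens less often. Requiring a supporting result on condomless acts before stopping would be a matter of preference. Its effect has not been calculated, and it is not needed here.
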